**Methods:**

To test our hypothesis, we are conducting a randomized, placebo-controlled clinical trial on 85 study participants who we stratify into two groups according to walking ability; those unable to walk (non-ambulatory group) and those able to walk (ambulatory group). The non-ambulatory group receives either daily AIH (15, 90s episodes at 10.0% O_2_ with 60s intervals at 20.9% O_2_) or daily SHAM (15, 90s episodes at 20.9% O_2_ with 60s intervals at 20.9% O_2_) intervention. The ambulatory group receives either 60-min walking practice (WALK), daily AIH + WALK, or daily SHAM+WALK intervention. Our primary outcome measures assess overground walking speed (10-Meter Walk Test), endurance (6-Minute Walk Test), and balance (Timed Up & Go Test). For safety, we also measure levels of pain, spasticity, systemic hypertension, and autonomic dysreflexia. We record outcome measures at baseline, days 5 and 10, and follow-ups at 1 week, 1 month, 6 months, and 12 months post-treatment.

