### Intervention

A.Duration

All participants enroll in 15 sessions at one of two site laboratories (1 baseline + 10 treatment days + 3 follow-up visits). Baseline (BL) evaluation occurs prior to the first day of intervention. Participants in each intervention group complete a total of ten days of intervention and 3 follow-up sessions (Fig. 1). If participants miss a treatment session, we do not conduct further assessments and exclude their data from analyses. However, if participants miss an assessment session, we record their data as “missing” at that time point.
B.Breathing treatment

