**Fig. 1 Fig1:**
[figure not shown]
Timeline of intervention and outcome measurements

Participants receive 10 treatment sessions of daily AIH or daily SHAM. A single AIH session consists of 15, 90s episodes of breathing at a fraction of inspired oxygen (FiO_2_) of 0.10 ± 0.02 with 60s intervals of 0.21 ± 0.02 FiO_2_ (room air). While a single daily SHAM session consists of 15, 90s episodes of 0.21 ± 0.02 FiO_2_ with 60s intervals of 0.21 ± 0.02 FiO_2_ (room air). We provide the treatments via a custom air delivery system; see [10, 23, 32–34] for details. In brief, the delivery system directs a known air mixture from either a pressure-swing absorption (PSA) system [HYP-123; Hypoxico Inc., USA] or a blower source to the non-rebreather facemask. For safety, oxygen concentration within the breathing circuit is continuously monitored [OM-25RME; Maxtec Inc]. Additionally, we continuously monitor blood oxygen saturation (SpO_2_) and heart rate (HR) at 1-s intervals, and blood pressure (BP) every 5th breathing interval using a MASIMO system [MASIMO rainbow SET, Irvine, CA].
C.Walking practice

Walking practice sessions immediately follow (within 10 min) the breathing intervention and last for 60 min. Walking practice involves intensive training in walking-related functional tasks using a skill-based training approach. Recent studies found skill-based walking practice is more consistent with community walking, providing meaningful gains in walking function after neurologic injury [35–37]. Task-based walking practice replicates environmental challenges encountered during real-world walking [36] and corresponds to gains in walking balance, speed, and endurance that can be measured using the timed-up and go (TUG), 10-m walk test (10MWT), and 6-min walk test (6MWT), respectively [37]. The walking practice incorporates activities to develop skills in 5 walking-related task domains: 1) walking balance (e.g., walking on different surfaces), 2) skilled walking (e.g., negotiating obstacles), 3) walking with a secondary task (e.g., walking and carrying object), 4) endurance, and 5) speed [37].

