Pain severity: Using the five-point Wong-Baker FACES scale of 0 (no pain) to 5 (extreme pain) [44, 45].Spasticity: Using the Spinal Cord Assessment Tool for Spastic Reflexes (SCATS) [46], and the cumulative sum of three SCATS subscales: clonus (0 = no spasticity; 3 = severe), flexor (0 = no spasticity; 3 = severe), and extensor (0 = no spasticity; 3 = severe); and spasms using the Penn Spasm Frequency Scale (PSFS) [47].Blood pressure: At all pre-post treatment/assessment and follow-up time points. For each participant we specifically record hypertension incident rate, i.e. number of hypertensive events divided by units of person-measures (the sum of the total number of BP measurements), which accounts for the total number of chances for detecting a hypertensive event and for measurements not made due to dropout or a disqualifying adverse event [48]. We will also compute relative risk for participants within each group, i.e. hypertension incidence rate in the daily AIH subgroup over that in the daily SHAM and/or WALK groups [49], respectively, with a relative risk of one indicating no association between systemic hypertension incidence with interventions.Autonomic dysreflexia incident rate i.e. number of autonomic dysreflexia events divided by the total person-time (number of study days completed by each participant) to account for the total number of chances for detecting autonomic dysreflexia for days not measured due to dropout or a disqualifying adverse event [48]. We also compute relative risk within each group, as autonomic dysreflexia incidence rate in the daily AIH group over the incidence rate in the daily SHAM and WALK groups, respectively [49].

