Daily AIH ± WALK does not induce maladaptive changes (spasticity, pain, systemic hypertension, autonomic dysreflexia) in persons with subacute SCI. First, we predict no difference in SCATS following daily AIH ± WALK as compared to daily SHAM±WALK or WALK. We also predict no difference in the changes in FACES scores between interventions. We anticipate daily AIH alone or combined with walking practice will not elicit greater incidence of systemic hypertension in persons with subacute SCI. To test this hypothesis, we will compare the incidence rates of hypertension between interventions (daily AIH, daily AIH + WALK, daily SHAM+WALK, WALK) using Relative Risk [49, 52]. A Relative Risk of one will indicate no association between systemic hypertension and interventions. Using the 95% confidence interval of the Relative Risk [49], we will determine if there is a statistically significant association between interventions. We predict the relative risk of hypertension comparing daily AIH vs. daily SHAM, daily AIH + WALK vs. daily SHAM+WALK, and daily AIH + WALK vs. WALK are not different. We also predict the incidences of autonomic dysreflexia comparing daily AIH vs. daily SHAM, daily AIH + WALK vs. daily SHAM+WALK, and daily AIH + WALK vs. WALK are not different.

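### The hypertension rate pools readings from before hypoxia, on treatment and at follow-up, which pulls mainly an acute post-breathing rise towards a relative risk of 1 in AIH versus SHAM

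*Protocol article*

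**What the plan says.** Under Outcome measures, blood pressure is taken "At all pre-post treatment/assessment and follow-up time points". The hypertension rate is the "number of hypertensive events divided by units of person-measures (the sum of the total number of BP measurements". No time window is set, the rate is not split by period, and no baseline or pre-session value is subtracted. The same section reads "a relative risk of one indicating no association between systemic hypertension incidence with interventions".

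Hypothesis 3 in Statistical analysis sets the decision rule: "Using the 95% confidence interval of the Relative Risk [49], we will determine if there is a statistically significant association between interventions". The prediction for hypertension covers AIH versus SHAM, AIH+WALK versus SHAM+WALK, "and daily AIH + WALK vs. WALK are not different".

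Four other statements determine which readings enter the rate:
- Intervention, A. Duration: "Baseline (BL) evaluation occurs prior to the first day of intervention".
- Intervention, B. Breathing treatment: sessions include "blood pressure (BP) every 5th breathing interval".
- Safety precautions, item D: vitals are taken before and after both the breathing and the walking sessions.
- Abstract, Methods: "The ambulatory group receives either 60-min walking practice (WALK), daily AIH + WALK, or daily SHAM+WALK intervention". WALK therefore has no breathing session.

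The autonomic dysreflexia rate has a similar form: events over all study days completed.

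**The concern.** AIH and SHAM participants follow the same measurement schedule, as do AIH+WALK and SHAM+WALK participants. A reading that carries no treatment effect has an expected ratio of 1 between such arms. Counting it in both numerator and denominator moves the pooled ratio towards 1. Baseline and day 1 pre-session readings cannot carry an effect of any kind. For a rise confined to the period after breathing, later pre-session and follow-up readings carry none either.

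The direction matters because Hypothesis 3 predicts no difference. A null result on acute hypertension could then come from the definition of the rate and not from safety. In-session monitoring and adverse event reporting would still pick up acute rises, but the article describes no comparison between arms there.

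AIH+WALK versus WALK is a different case. The AIH+WALK arm has extra readings around breathing, so the mix differs by design. If risk differs between resting and post-walk readings, the ratio leaves 1 without any AIH effect, in a direction that cannot be fixed in advance.

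**Working it through.** The protocol gives no hypertension rate, expected relative risk, margin or power, so there is no planned figure to reproduce. Its sample-size calculations concern walking outcomes only.

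**Inputs from the protocol.** One baseline, ten treatment sessions, and three follow-up visits (Intervention, A) or four (Abstract). Vitals are taken before and after each session. During breathing, 15 episodes / 5 × 10 sessions = 30 readings.

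**Assumed, because the schedule table is not shown.** 2 baseline + 20 around treatment + 4 at the day 5 and day 10 assessments + 6 or 8 at follow-up = 32 or 34 readings. Background risk is equal at all readings unless varied.

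**Formula.** If *a* of *m* readings carry a true relative risk R, the pooled ratio is 1 + (a/m)(R − 1). At R = 2 this is 1 + a/m.

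**AIH versus SHAM, true relative risk 2**

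| Effect | Affected / total | Apparent |
|---|---|---|
| Acute, after breathing | 10/34, 10/32 | 1.29–1.31 |
| Same, 3 pre-exposure readings dropped | 10/31, 10/29 | 1.32–1.34 |
| Acute, readings during breathing counted | 40/64, 40/62 | 1.63–1.65 |
| Same, 3 pre-exposure readings dropped | 40/61, 40/59 | 1.66–1.68 |
| Lasting the two treatment weeks | 23/34, 23/32 | 1.68–1.72 |
| Lasting to 12 months | 31/34, 29/32 | 1.91 |

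The 3 pre-exposure readings are 2 at baseline and 1 before the day 1 session. The 23 are 10 post-session, 9 later pre-session and 4 assessment readings.

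**Sensitivity.** Without the four day 5 and day 10 assessment readings the total is 28 or 30, and the acute doubling appears as 1 + 10/28 = 1.36 or 1 + 10/30 = 1.33. With 28 readings and background risk at the other 18 equal to *k* times that after breathing, the ratio is (20 + 18k)/(10 + 18k): 1.53 at k = 0.5 and 1.22 at k = 2.

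**AIH+WALK versus SHAM+WALK, acute doubling.** Ten post-walk readings are added.
- Basic schedule: 10/44 and 10/42 give 1.23–1.24.
- With readings during breathing: 40/74 and 40/72 give 1.54–1.56.
- With an assumed 5–10 readings per walking session as well: 40/174 to 40/122 give 1.23–1.33.

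**AIH+WALK versus WALK, no AIH effect.** Let post-walk risk be *w* times resting risk. With the 34-reading schedule the ratio is [(34 + 10w)/44] / [(24 + 10w)/34], which is 0.948 at w = 2 and 1.039 at w = 0.5. With readings during breathing it is [(64 + 10w)/74] / [(24 + 10w)/34], which is 0.877 and 1.093. The 32-reading schedule gives 0.943, 1.044, 0.868 and 1.103.

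**Dysreflexia doubled on the ten treatment days.** (5 + 20)/15 = 1.67 over 15 study days, and (4 + 20)/14 = 1.71 over 14.

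**Chance that the 95% interval lies wholly above 1.** Simulated for AIH versus SHAM at relative risk 2, with 20,000 trials per case. Each arm has 15 participants (34 × 0.88 / 2 ≈ 15). Assumed: 10% background risk, within-person correlation 0.05, and a log rate ratio with a between-participant standard error.

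| Effect | Pooled rate | On-treatment readings only |
|---|---|---|
| Acute | 15% | 46% |
| Acute, readings during breathing counted | 45% | 69% |
| Two-week | 44% | 47% |
| 12-month | 61% | 47% |

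On-treatment means post-breathing readings, plus those during breathing in the second row. Dropping only the pre-exposure readings from the pooled rate gives 17% and 47% in the first two rows. For a 12-month effect, a rate from later pre-session and follow-up readings gives 61%. Against SHAM+WALK, the pooled rate detects an acute doubling in 12%, in 38% with readings during breathing, and in 14–21% if walking readings count too.

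Over backgrounds of 5–20% and correlations of 0.02–0.10, the acute AIH versus SHAM case gives 9–39% pooled against 21–91% post-breathing. With readings during breathing it gives 18–96% against 29–100%.

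**The case against.** **The target is lasting harm.** Aim 3 concerns maladaptive change and pathology, and the Discussion stresses enduring effects. For a lasting effect the pooled rate does well: 1.91, with 61% power. This stands and limits the point to acute rises. Post-treatment readings are collected for this very outcome, however, so the acute question belongs to the plan.

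**The part that is wrong under any target is small.** Dropping the pre-exposure readings alone moves 1.29–1.31 to 1.32–1.34 and power from 15% to 17%. This stands; most of the dilution comes from later pre-session, assessment and follow-up readings.

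**The event definition is unsettled.** Adverse event reporting speaks of a change in systolic pressure to above 140 mmHg. If that means new onset, pre-exposure readings yield few events, and the acute ratio is 1.32–1.34 (two-week 1.74–1.79). If it means a change from before to after a session, about 16–17 post-session readings can yield events, 10 of them after breathing, and the ratio is about 1.6. Dilution is smaller but remains. It would vanish only if readings unaffected by breathing never produced events. The denominator is described as counting chances to detect an event, which suggests that all readings can.

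**The size rests on assumptions.** The schedule, background risk and correlation are not given, and the interval method comes from a cited source that is not shown. This stands. The direction for AIH versus SHAM does not depend on these inputs.

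**A condensed article leaves period splits to the full plan.** A split may exist there. But the article states the rate, its denominator and the decision rule explicitly, and the point is about that stated rule.

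**Conclusion.** The concern holds. As defined, the pooled rate understates an acute post-breathing rise in AIH versus SHAM, with or without WALK, and so favours the predicted result. On the assumed schedule with equal background risk, an acute doubling appears as about 1.3 in AIH versus SHAM, or about 1.6 if readings during breathing count. A two-week effect has its estimate diluted with little loss of power, and a 12-month effect is barely changed.

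Against WALK alone the distortion is about 0.87 to 1.10 if post-walk risk is twice or half the resting risk, with the direction unknown. The dysreflexia dilution is modest.

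The point is minor to moderate. It limits what Aim 3 can conclude about acute hypertension and does not invalidate the aim. Confidence in the direction for AIH versus SHAM is good. Confidence in the size is moderate, because the reading counts and background risks are assumed.

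**What to change.** - Exclude baseline and day 1 pre-session readings from the rate, and use baseline blood pressure as a covariate.
- Report two relative risks: (a) on-treatment readings, and (b) later pre-session and follow-up readings. Keep the pooled rate as descriptive.
- For AIH versus SHAM and AIH+WALK versus SHAM+WALK, build (a) from readings during and directly after breathing, before walking practice.
- For AIH+WALK versus WALK, use only time points taken in both arms: directly before and after walking practice on treatment days, and follow-up. Show the before-walk reading on its own. Pooled with the after-walk reading, an acute doubling seen only before walking appears as (20 + 10w)/(10 + 10w), which is 1.33 at w = 2, 1.50 at w = 1 and 1.67 at w = 0.5.
- Split the dysreflexia rate into treatment days and follow-up days.

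The cost is analysis wording, since the protocol already takes these readings; the matched time points for WALK need to be named. The downside is fewer readings per rate and two comparisons in place of one. From post-breathing readings alone, rate (a) has less power for a lasting effect than the pooled rate and gains almost nothing for a two-week effect, so it should be read together with rate (b).

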### Statistical analysis

To advance our understanding and the applicability of daily AIH-induced walking recovery, we plan to test three sub-hypotheses using parametric and non-parametric statistical inferencing. Statistical significance corresponds to a p-value less than 0.05.

#### Hypothesis 1

Daily AIH improves walking recovery in persons with subacute SCI initially unable to walk as compared to daily SHAM. We plan to quantify the success of completing walking skills using our primary outcome measures (i.e., TUG, 10MWT, and 6MWT) by a recovery score of 0–3. We predict that the number of walking skills recovered will be greater for participants receiving daily AIH vs daily SHAM, indicating improved walking ability. We will use a Friedman two-way (factor 1 = intervention: daily AIH, daily SHAM; factor 2 = time: baseline, mid-test, post-test, and follow-ups) repeated measures analysis of variance (ANOVA) by ranks to compare walking recovery between and within groups. If there are significant differences, we plan post-hoc tests for pairwise comparisons [50]. We also anticipate that improvement in walking recovery will correlate with improved SCI-FAI, WISCI and LEMS scores, suggesting clinical relevance of daily AIH as an intervention across various SCI impairment levels.

#### Hypothesis 2

Daily AIH + WALK improves walking ability in ambulatory persons with subacute SCI as compared to daily SHAM+WALK and WALK. We predict a decrease in 10MWT and TUG time and an increase in 6MWT distance relative to baseline following dAIH+WALK (vs. dSHAM+WALK, WALK). We will test three related sub-hypotheses using a linear mixed model with fixed effects [51]. We will use intervention (daily AIH + WALK, daily SHAM+WALK, WALK) and time (day) as the fixed main effects, with subject as random effect, while scores for TUG (time), 10MWT (time), and 6MWT (distance) will be considered as repeated measures. Differences from baseline scores will be compared between and within interventions at mid-test, post-test, and follow-ups. If ANOVAs reveal significant differences, we will use the Tukey-Kramer post-hoc test to identify pairwise differences. If baseline measures are significantly different between intervention groups, we plan to use an analysis of co-variance (ANCOVA) to analyze these data.

#### Hypothesis 3

Daily AIH ± WALK does not induce maladaptive changes (spasticity, pain, systemic hypertension, autonomic dysreflexia) in persons with subacute SCI. First, we predict no difference in SCATS following daily AIH ± WALK as compared to daily SHAM±WALK or WALK. We also predict no difference in the changes in FACES scores between interventions. We anticipate daily AIH alone or combined with walking practice will not elicit greater incidence of systemic hypertension in persons with subacute SCI. To test this hypothesis, we will compare the incidence rates of hypertension between interventions (daily AIH, daily AIH + WALK, daily SHAM+WALK, WALK) using Relative Risk [49, 52]. A Relative Risk of one will indicate no association between systemic hypertension and interventions. Using the 95% confidence interval of the Relative Risk [49], we will determine if there is a statistically significant association between interventions. We predict the relative risk of hypertension comparing daily AIH vs. daily SHAM, daily AIH + WALK vs. daily SHAM+WALK, and daily AIH + WALK vs. WALK are not different. We also predict the incidences of autonomic dysreflexia comparing daily AIH vs. daily SHAM, daily AIH + WALK vs. daily SHAM+WALK, and daily AIH + WALK vs. WALK are not different.

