#### Randomization and stratification

We stratify eligible participants into either an ambulatory or a non-ambulatory group based on their initial walking function. The ambulatory group includes eligible participants who successfully complete one of the following without human assistance: TUG, 10MWT, or 6MWT without human assistance. Participants enrolled in the non-ambulatory group are unable to complete any of these assessments at initial screening. Prior to enrollment of the first study participant, a research statistician generated the balanced, randomization scheme for treatment allocation in both non-ambulatory and ambulatory groups using the R Statistical Package [29]. Using this scheme, the clinical coordinator assigns each participant to their respective treatment group using their alphanumeric identifier.

Although we inform participants about their group, we blind them to the treatment they receive (i.e. daily AIH or daily SHAM). The clinical raters, trainers, and data analysts are also unaware of the treatment that each participant receives during after the trial. We plan to rigorously quantify our blinding methods. Participants guess the breathing intervention received at the end of each treatment day and indicate guess confidence using a Likert scale [30, 31]. Using a contingency table and Fischer’s Exact Test, we will determine if the probability of correct guessing is different from chance. Using multivariate logistic regressions, we also will assess factors that may influence guessing (e.g., adverse events, perceived effects, and sensorimotor changes).

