**Table 3 Tab3:**
[figure not shown]
Timeline for clinical assessments and outcome measurements

We ensure a minimum of 5-min for rest breaks between tests. Participants able to ambulate attempt two trials each for the TUG and 10MWT (at their fastest, but comfortable and safe speed) with a minimum of 1-min rest between trials. The average TUG time and 10MWT speed for the two the trials will be used for analyses. Participants will attempt a single trial of the 6MWT at their fastest yet comfortable walking speed that is sustainable for six minutes, while distance covered at 2 and 6-min time points is recorded. We quantify success of completing each of the tests using a recovery score of 0–3 (0 = complete, 1 = attempted test, 2 = partially recovered but failed to complete; 3 = fully recovered). We also record secondary outcome measures of walking function that include the Walking Index for Spinal Cord Injury (WISCI) II [42] and SCI Functional Ambulation Index (SCI-FAI) [43].

To quantify maladaptive changes that may potentially occur following daily AIH exposure, we measure the magnitude and frequency of pain, spasticity, systemic hypertension, and autonomic dysreflexia during our assessments.

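### The Friedman test named for Hypothesis 1 gives no valid AIH-versus-SHAM comparison, whether participants or visits are the blocks

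*Protocol article*

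**What the plan says.** The arms of Aim 1 are parallel. The abstract's Methods paragraph says "The non-ambulatory group receives either daily AIH" or daily SHAM, and Randomization and stratification describes a "balanced, randomization scheme for treatment allocation in both non-ambulatory and ambulatory groups". No crossover or matching is described.

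Hypothesis 1 is a between-arm claim: "We predict that the number of walking skills recovered will be greater for participants receiving daily AIH vs daily SHAM". The only test named for it is: "We will use a Friedman two-way (factor 1 = intervention: daily AIH, daily SHAM; factor 2 = time: baseline, mid-test, post-test, and follow-ups". The sentence continues that this is a "repeated measures analysis of variance (ANOVA) by ranks to compare walking recovery between and within groups". Further testing is conditional: "If there are significant differences, we plan post-hoc tests for pairwise comparisons".

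The outcome is a 0–3 recovery score for each walking test. Outcome measures gives its key as "0 = complete, 1 = attempted test, 2 = partially recovered but failed to complete; 3 = fully recovered".

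Three other statements bear on the point. Sample size bases Aim 1 on a non-parametric comparison between the two interventions. Hypothesis and aims expects spontaneous neural recovery alongside any AIH effect. Intervention (Duration) keeps a participant who misses an assessment and records that visit as missing.

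**The concern.** The two ways in Friedman's two-way analysis by ranks are block and condition. It is a one-factor test with blocking. It is not a two-factor design in which one factor varies between people and the other within them. In Aim 1, intervention varies between participants and time varies within them, so the two factors listed do not fit the named test.

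At stake is the efficacy conclusion of Aim 1. If the test is significant because people recover in the months after injury, the result may be reported as an AIH effect. If the software is set up the other way round, the arms are compared with the wrong error rate. Separately, the score being ranked has a key in which completing a test appears to fit both its lowest and its highest level.

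**Working it through.** **Inputs.** From Sample size: N = 34 including 12% attrition, effect size 0.84, ρ = 0.4, α = 0.05. Evaluable participants: 34 × 0.88 = 29.9, about 30, or 15 per arm if allocation is 1:1 (assumed from the balanced scheme). From the abstract: baseline, days 5 and 10 and four follow-ups, so 7 time points. Intervention (Duration) gives three follow-ups, which would make 6; the argument does not depend on which is right.

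**The plan's own figure.** The stated N is consistent with a between-arm F test in a repeated-measures ANOVA, with non-centrality λ = f²·N·m / (1 + (m − 1)ρ). Take f = 0.84/2 = 0.42, ρ = 0.4 and m = 3 (an assumption, borrowed from Aim 2). At N = 30, λ = 0.1764 × 30 × 3 / 1.8 = 8.82. The critical value of F with 1 and 28 df is 4.20, and power is 0.818. Then 30 × 1.12 = 33.6, or 34. (The printed f = 0.6 with m = 3 gives 16, or 19 after attrition; that discrepancy is outside this point.) The sizing therefore looks to a between-arm comparison.

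**Reading 1: participants as blocks.** The statistic is Q = 12 / [n·k(k + 1)] · ΣRⱼ² − 3n(k + 1). Here n is the number of participants, k the number of visits, and Rⱼ the sum over participants of the within-person rank at visit j. Adding a constant to all of one person's scores leaves that person's ranks unchanged, so a constant arm difference drops out. Check with 15 + 15 participants and 7 visits: Q = 9.214. After adding 5 to every score in one arm, Q = 9.214 again.

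An arm difference that appears only after baseline does enter Q, but merged with everyone's change over time. Simulation: latent score = person effect (SD 1) + linear trend over the visits + noise (SD 0.7), cut at 0.8, 1.4 and 2.0 into 0–3; baseline set to 0; 15 per arm; 1,500 trials per row. The rank-sum test is on change from baseline to the last visit.

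| Scenario | Pooled Friedman significant | Between-arm rank-sum significant |
|---|---|---|
| No AIH effect, common trend 1.5 | 100% | 4.6% |
| No AIH effect, milder common trend 0.75 | 100% | 4.3% |
| AIH shift 1.0 after baseline, common trend 1.5 | 100% | 48% |

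The Friedman column is the same with and without an AIH effect.

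Running the test separately in each arm does not help. In the milder-trend null scenario it was significant in 86% and 88% of trials in the two arms, and in exactly one arm in 24%. Significance in one arm but not the other is thus common when nothing differs.

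**Reading 2: visits as blocks, participants as replicates.** Ranks are now taken across participants within each visit, so the arms are compared. The null distribution, however, treats up to seven scores from one person as independent. With no AIH effect (2,000 trials, assumed latent model):

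| Within-person latent correlation | False-positive rate |
|---|---|
| 0.4 (the ρ in Sample size) | 22% |
| 0.6 | 30% |
| 0.8 | 36% |

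A rank-sum test on participant means stayed at 4–5%. Other runs of this reading under similar assumptions gave 23–34% and 27–31%.

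**Missing visits.** The standard participant-blocked test needs complete blocks. A participant with one missed assessment is kept under Intervention (Duration) but would drop out of this test.

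**Score key.** Level 2 is partial recovery without completing the test, and level 3 is full recovery, so the scale rises with recovery. Level 0, below both, is labelled complete. Read literally, a completed test fits 0 and 3, and the direction of any rank analysis depends on which is used.

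**The case against.** The best defence is that the article never says participants are the blocks. It names intervention and time as the factors, and the replicated form of the test, with visits as blocks, does compare the arms. This stands in part: it is too absolute to say that the named test cannot compare the arms, since that holds only with participants as blocks. It does not rescue the plan, because the replicated form rejects a true null in roughly 20–35% of trials.

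It can also be said that the post-hoc tests might include arm comparisons, or that a statistical analysis plan may clarify. The post-hoc tests run only after a significant Friedman result, so they inherit its fault. The text states a test and its factors, so this is not detail left to another document.

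Four stronger readings are tempting, and the documents do not support them.
- A reader might infer that a real AIH effect would go undetected. Baseline is among the time levels, so an effect arising after baseline is itself a change over time and the participant-blocked test tends to reject. The fault is that it rejects without AIH too.
- A reader might infer that everyone starts at score 0 by definition. Randomization and stratification says only that these participants cannot complete any of the tests, which also fits levels 1 and 2.
- A reader might infer that Aim 1 is unanswerable. The randomised data can answer it; only the named test fails.
- A reader might object that the prediction counts recovered skills while the score runs 0–3. How the three per-test scores are combined is detail that an article may leave to the full protocol.

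**Conclusion.** The concern holds: the one test named for Hypothesis 1 is wrong for a parallel-arm comparison under either reading.

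With participants as blocks, the loss of a constant arm difference is exact and needs no model. The rejection rate of about 100% without an AIH effect is model-based: an ordinal 0–3 score, 15 per arm, 7 visits, baseline at 0 and clear recovery in both arms. Less recovery, or baseline scores above 0, could lower it. It would still measure recovery over time and not the effect of AIH. With visits as blocks, the false-positive rate of roughly 20–35% against a nominal 5% rests on assumed within-person correlations of 0.4 to 0.8.

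This must be corrected before analysis. The score key is a separate, secondary defect. It is probably a wording slip, but as printed it leaves the direction of the outcome unclear.

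**What to change.** In Statistical analysis, Hypothesis 1, replace the Friedman test with a rank or ordinal method that has a between-participant arm factor and accounts for repeated measures. Two suitable choices are a Brunner-Langer F1-LD-F1 analysis and a proportional-odds mixed model with arm, visit and arm-by-visit terms. State that the Hypothesis 1 conclusion rests on the between-arm test or on the arm-by-visit test, say which, and make any pairwise tests follow from it. The chosen method should use participants with a missed assessment, in line with Intervention (Duration). Naming a single primary visit or a total over the three tests is optional and not needed to cure the error.

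In Outcome measures, reconcile the label of level 0 with those of levels 2 and 3 so that the score runs in one direction, and check that scores already recorded follow the same key.

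The cost is analysis wording and a corrected key. No new data or change of design is needed.
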